#### Recruitment

Partner nutrition practitioners advised on and assisted with the community engagement process to invite store directors in each of their regions. Nutrition practitioners and/or the research team (where required), provided store directors/owners either directly or via their store manager(s) and/or area managers with an invitation to participate, including information about the project (short video or flyer), project information sheet and consent form. These were delivered in person or via email. Follow-up contact with the store owners/manager(s) was made by the nutrition practitioner and/or research team to arrange a meeting (face-to-face, or via videoconference) to explain the study, its purpose and consent procedure, in detail. For some stores, store managers and/or store group area managers were also involved. This was to arrange a suitable time for the meeting and to communicate study detail to Aboriginal and Torres Strait Islander store directors to ensure free and fully informed consent. Where required and within two-weeks of the meeting, a follow-up phone call was made to the store owner(s)/manager(s) by the nutrition practitioner and/or research officer to inquire on their decision. Phone contact up to three times if needed was allowed. We have found these methods for store recruitment to be acceptable to communities [4, 71].

## Methods: assignment of interventions (for controlled trials)

### Allocation

Computer generated random numbers were used to allocate stores in near equal numbers to intervention/control within the store group serviced by each partner organisation (i.e., ALPA, NT Health (Central Australia), NT Health (Top-End), Katherine West, Miwatj, Outback Stores). Two stores with ALPA and two stores serviced by Miwatj were forced as each of these store pairs were in the same community and so 15 stores were allocated to intervention and 17 to control. Allocation occurred simultaneously after the required sample of stores was reached.

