## Methods

This is a store-level pragmatic randomised parallel group, 2-arm, superiority trial with a 1:1 allocation. The study commenced in 2022.

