#### Sample size

There are 53 eligible stores in 45 communities across the NT serviced by the partner s. We anticipate from previous trials an 85% consent rate and no withdrawals (or loss to follow up for the primary outcome). A sample of 36 communities will have 90% power to detect an ~ 3.5% lower percentage change in the primary outcome, free sugars g/MJ (SD of % change = 3%). The mean effect size of an ~ 3.5% reduction in free sugars (g/MJ) is based on our Healthy Stores 2020 trial [4]. We commenced recruitment in 2022 and recruited 32 stores (Fig. 1 and Additional Table 1).

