### Analysis and statistical methods

The data source for analysis of the primary outcome and some secondary outcomes is weekly sales reports provided by the stores. Unique store products are linked, using rule-based algorithms, machine learning and human verification, to nutrient data derived from the Australian Food, Supplement, and Nutrient Database, with discretionary food flagged from the Discretionary Food List developed by the Australian Bureau of Statistics [74, 75]. We use built-in, reliable data checking processes developed over the last decade in our research to assess and quantify the nutritional impact of sales.

Following data aggregation, the outcomes will be log-transformed. The main analysis for an outcome will be a simple ANCOVA analysis using sales data from July to December 2021 and 2023, and randomisation group for the primary outcome.

We anticipate that the impact of the intervention will be both immediate and gradual. In stores that receive the benchmarking intervention, we estimate an immediate 3.5% reduction in free sugars to energy purchased as a result of food retail practice change. A reduction in free sugars to energy at this level from the baseline shown in the Healthy Stores 2020 trial has been shown to be the equivalent to an approximate 10% lower risk for cardiovascular disease mortality [4]. We then expect a more gradual effect at the broader remote store level post-intervention as the benchmarking model is scaled up into policy and practice by different jurisdictions for the benefit of all remote communities, if found to be adoptable and effective.

Implementation fidelity will be assessed according to i) proportion of partner organisation representatives completing training; and, ii) annual benchmarking cycles fully completed in specified timeframes. Data will be collected on action plans and the resource input to their implementation.

Change in store best-practice policy action adoption and practice implementation with time will be described and used to interpret results of primary and secondary outcomes. Food price and Environment Scan survey results will be described for context.

Policy Action Assessment: Proportion of policy actions by adoption status (fully adopted, partially adopted, getting started, not yet started) for 2022, 2023 and 2024 for each intervention store will be calculated and any differences with time described.

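### Two same-community store pairs were forced at allocation, but the named ANCOVA has no community unit or cluster term, so the analysis unit needs fixing

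*Protocol article*

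**What the plan says.** The unit changes from section to section of the protocol article.

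- **Methods, opening paragraph:** "This is a store-level pragmatic randomised parallel group, 2-arm, superiority trial with a 1:1 allocation".
- **Sample size:** "A sample of 36 communities will have 90% power to detect an" a difference of about 3.5% in percentage change, with an SD of 3%. The same section gives 53 eligible stores in 45 communities and reports 32 recruited stores.
- **Allocation:** random numbers were used to "allocate stores in near equal numbers to intervention/control within the store group serviced by each partner organisation", with six partner groups listed. The exception is "Two stores with ALPA and two stores serviced by Miwatj were forced as each of these store pairs were in the same community", with the result that "15 stores were allocated to intervention and 17 to control".
- **Analysis and statistical methods:** "Following data aggregation, the outcomes will be log-transformed". The level of aggregation is not given. Then: "The main analysis for an outcome will be a simple ANCOVA analysis using sales data from July to December 2021 and 2023, and randomisation group". No community term, cluster adjustment or partner stratum is named.

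**The concern.** The investigators judged that two stores in one community could not be allocated independently of each other, but nothing in the named analysis carries that judgement forward. Paired stores plausibly share shoppers, supply conditions and local events, so their changes in free sugars per MJ may be correlated. If the rows of the ANCOVA are stores and a pair sits in one arm, the model counts two independent observations where one unit was allocated.

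A second question hangs on one word. Forced may mean that the second store of a pair followed a random draw made for the community, or that the pair's arm was chosen. In the latter case 4 of 32 stores (12.5%) would enter the primary comparison without randomisation. The article does not say which.

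**Working it through.** **Inputs.** From the article: difference 3.5%, SD 3%, 36 communities planned, 32 stores recruited, 15 v 17, two forced pairs. Assumed, because not stated: two-sided alpha 0.05; within-pair correlation rho of the change, shown as a range; no shared community other than the two pairs, so 32 − 2 = 30 communities.

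**The plan's own figure.** A two-sample comparison of means at 90% power needs 16 per arm (32) by the normal approximation and 17 per arm (34) by the noncentral t. At 18 per arm, power is 93.8% (normal) or 92.5% (t). The stated 36 communities is reproduced, slightly on the generous side. For 32 independent stores split 15 v 17, power is 90.9% (normal) or 89.0% (t).

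**Effect of the pairing alone.** With p_I and p_C same-arm pairs in intervention and control,

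Var(difference) = SD² × [(15 + 2·p_I·rho)/15² + (17 + 2·p_C·rho)/17²].

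With independence: 9 × (1/15 + 1/17) = 9 × 0.1255 = 1.129, SE 1.063.

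Both pairs in control (p_C = 2), rho 0.6: 9 × [1/15 + (17 + 2.4)/289] = 1.204, SE 1.097. At rho 0.9: 9 × [1/15 + (17 + 3.6)/289] = 1.242, SE 1.114.

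Ratio of true SE to the independent-store SE, by placement of the pairs:

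| rho | both in control | one in each arm | both in intervention |
|---|---|---|---|
| 0.3 | 1.016 | 1.019 | 1.021 |
| 0.5 | 1.027 | 1.031 | 1.035 |
| 0.9 | 1.048 | 1.055 | 1.062 |
| 1.0 | 1.054 | 1.061 | 1.069 |

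The residual variance is also slightly underestimated, which takes the ceiling at rho 1 to 1.073.

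**Type I error of the store-level test.** Simulated null trials with a pooled t-test and both pairs in control gave 5.0% (rho 0), 5.4% (0.3), 5.8% (0.6) and 6.2% (0.9). With one pair in each arm the figure at rho 0.9 was 6.3%. Null simulations of the ANCOVA with a baseline covariate gave about 5.6% at rho 0.5 and 6.0% to 6.9% at rho 1, depending on placement.

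**If the pairs were split across arms.** The covariance then enters with a negative sign: Var = 9 × [1/15 + 1/17 − 4·rho/(15 × 17)]. The true SE is 0.968 of nominal at rho 0.5 and 0.935 at rho 1. Simulated type I error falls to 4.3% and 3.5%.

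**Adding the omitted strata.** With six assumed strata of 5 to 6 stores, same-arm pairs and no stratum term in the model, null simulations gave:

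| Stratum ICC (assumed) | rho 0.6 | rho 0.9 |
|---|---|---|
| 0 | 5.7% | 6.4% |
| 0.05 | 5.5% | 5.7% |
| 0.1 | 4.8% | 5.3% |
| 0.2 | 4.0% | 4.3% |

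**Power under the alternatives (noncentral t, 3.5%, SD 3%).** Summed to 30 communities: 86.9% (15 v 15, both pairs in control), 86.8% (14 v 16, one in each arm), 86.4% (13 v 17, both in intervention). With the four forced stores dropped, for example 15 v 13, power is about 84%.

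**The case against.** The article never says that 32 stores are analysed as independent rows. It leaves the aggregation level open, states power per community, and is a condensed account whose analysis plan is not shown, so a community-level analysis would be consistent with it. Nor does it say that each pair went to a single arm. Both points stand, and they make the statistical consequence conditional. They do not remove the inconsistency: the article fixes the model and reports the allocation, and it uses different units for power and allocation without saying which one the model uses. Same-arm placement is also the more natural reading, since forcing is offered as the reason for 15 v 17, and splitting a pair would not by itself create an imbalance.

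Only 4 of 32 stores are affected, and the correlation has no source in the article. Shoppers switching between two stores could even give opposite changes. That stands too: the effect is small and its sign is assumed.

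Giving each store equal weight is a legitimate choice in a store-level trial where each intervention store receives its own feedback report and action plan. Double weight for a two-store community is therefore not in itself an error.

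A reader might infer that the planned confidence intervals are too narrow and the type I error is above 5%. The article does not support that as a flat statement. The same ANCOVA leaves out the partner strata, and a modest stratum effect cancels or reverses the inflation. A reader might also infer that four stores were not randomised. The wording leaves that open and does not establish it.

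**Conclusion.** The mismatch between the unit of power, the unit of allocation and the named model is real and should be resolved. Its size is modest. For a store-level ANCOVA with same-arm pairs and positive correlation, the pairing alone makes the true SE about 2% to 5% larger than the model's when both pairs are in control and rho is 0.3 to 0.9 (up to about 6% if both are in intervention), with a ceiling near 7% at rho 1. Type I error is about 5.4% to 6.3% with both pairs in control or one in each arm. This would matter for a borderline result and is unlikely to matter otherwise.

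The figures rest on an assumed rho, same-arm placement, stores as rows and no stratum effect. With the strata taken into account the net direction is not known, and with pairs split across arms it reverses. Whether each pair's arm was drawn at random is a separate question that only the investigators can answer, and it may matter more than the standard error.

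**What to change.** 1. Make the allocated unit the analysis unit and say so. Either sum free sugars and energy over the two stores of each shared community, take the ratio, and run the ANCOVA on about 30 communities; or keep stores as rows with a community random effect or a small-sample cluster-robust standard error, which preserves store-level weighting.
2. Include the partner strata used in allocation in the model.
3. State which arm each pair entered and whether that arm was drawn at random for the pair as a unit. If it was not, add a sensitivity analysis without the two pairs.
4. Restate the sample size and the recruited number in the same unit.

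The cost is wording and one aggregation or modelling step, with no new data. Summing the pairs lowers power from about 89% to 86–87% at the planned effect and changes the weighting from stores to communities. The stratum terms use a few degrees of freedom. The sensitivity analysis, if needed, would have about 84% power with, for example, 15 v 13 stores.

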### Blinding

Those analysing the outcomes will be blinded. Blinding is not possible for other members of the research team, data collectors, partner representatives and participating stores.

## Methods: data collection, management, and analysis

Data collection methods are described in Table 1. Research practice against the ‘CREATE Tool’ is reported in Table 2.

**Table 2 Tab2:** Research practice considered against the CREATE Tool best-practice guidance

CREATE TOOL practice	Benchmarking for healthy remote stores in remote Aboriginal and Torres strait islander communities—research practice
1.Does the research respond to a need or priority determined by the community?	This research responds to a call made publicly through the 2020 Parliamentary Inquiry into food pricing and food security in remote Indigenous Australia, by remote Aboriginal and Torres Strait Islander food retail organisations, Aboriginal and Torres Strait Islander health services and academics for benchmarking to standardise health-enabling retail practice for the benefit of all communities [2]. It builds on the decades of collaborative and reciprocal research that Aboriginal and Torres Strait Islander communities have informed and contributed to with members of the author group, and brings together Indigenous and non-Indigenous academics and partners who have worked with remote communities for many years to address inequities in access to healthy and affordable food. It is informed specifically by a continuous improvement approach to improving food security in remote communities that was developed in 2009–2013 with four remote Aboriginal and Torres Strait Islander communities and other stakeholders [39, 40]. It seeks to ultimately strengthen the decision-making capacity of Aboriginal and Torres Strait Islander store owners/directors in tackling the devastating impact on health experienced by Aboriginal and Torres Strait Islander Peoples in remote communities from a rapid change to the food environment, especially the ready availability of energy-dense, nutrient-poor discretionary foods and beverages. This research takes a strengths-based approach to influence diet as a social determinant of health and wellbeing and in doing so aligns directly with two of the three priority research areas of the National Health and Medical Research Council Road Map 3: A strategic framework for improving Aboriginal and Torres Strait Islander Health through research and with the National Agreement Closing the Gap Priority Reform 4 “Improve and share access to data and information to enable Aboriginal and Torres Strait Islander communities make informed decisions” [72, 73].
2.Was community consultation and engagement appropriately inclusive?	Consultation in the grant writing and project planning processes occurred with several Aboriginal organisations including ACCHOs and ALPA, and government and Outback Stores. These partners then worked with the research team to inform Aboriginal and Torres Strait Islander directors and private store owners of the study and invite their participation. To uphold trustworthiness we approached Aboriginal and Torres Strait Islander store directors by presenting on the study at one of their board meetings and gave appropriate time for a collective board decision. All partners were invited to participate in the structures established for co-design of the benchmarking with continuous improvement model and research processes. Aboriginal and Torres Strait Islander community members contributed to the co-design of the Benchmarking strategy through workshops
3.Does the research have Aboriginal and Torres Strait Islander research leadership?	Three of the ten project Chief Investigators are senior Aboriginal leaders and academics. Aboriginal and Torres Strait Islander leadership is also provided through the Associate Investigator group and the partner organisations
4.Does the research have Aboriginal and Torres Strait Islander governance?	The project is designed with multiple levels of governance. The Chief Investigator group oversees a project benchmarking co-design committee that has representatives from all partner organisations, the Chief Investigator group and the research team. Four task groups comprising members from the benchmarking co-design committee feed in to the benchmarking co-design committee and have responsibility for the co-design of the benchmarking model and data collection tools and research processes. The partner organisations are the face of the research with participating stores and liaise with store directors ensuring local community protocols are respected and followed. The Chief Investigator group with the project lead guides the research team who coordinates the research activity and delivery of study milestones
5.Are local community protocols respected and followed?	We are advised by our partners and Aboriginal and Torres Strait Islander store directors on community protocols and when it is a suitable time to visit the community and/or meet with Aboriginal and Torres Strait Islander store directors. Written permits are required under Commonwealth and Territory law to enter Aboriginal land. The Northern Land Council is responsible for administering the permit system for traditional owners in the Top End, and the Central Land Council for traditional owners in Central Australia, Northern Territory. Permits are therefore obtained prior to visiting Aboriginal Land by the research team and partners. All endeavour is taken to remain flexible with the implementation of the research to ensure there is no adverse impact on other community priorities. For example, meetings will be rescheduled if this is advised by store directors and/or partner representatives We conduct our research with a commitment to the spirit and integrity of Aboriginal and Torres Strait Islander Peoples and demonstrate a high regard and respect for the welfare, rights, beliefs, perceptions, customs and cultural heritage of both the individual participants involved in our research and the community as a collective
6.Did the researchers negotiate agreements in regards to rights of access to Aboriginal and Torres Strait Islander peoples’ *existing* intellectual and cultural property? 7.Did the researchers negotiate agreements to protect Aboriginal and Torres Strait Islander peoples’ ownership of intellectual and cultural property *created* through the research?	A multi-institutional agreement (MIA) for the project has been negotiated between all participating research institutions and partners, outlining the funding allocation, each organisation’s role, contribution, and ownership/custodianship and use of background and project created intellectual property. Data remain the property of the community and store directors/owners with investigators and partners being the custodians The study consent form ensures that participants provide consent knowing that ownership of Aboriginal and Torres Strait Islander knowledge and cultural heritage is retained by participants should this be shared (although it is likely due to the nature of the project that this type of information is not shared). This is also a requirement of the Human Research Ethics Committee with oversight for this project
8.Did Aboriginal and Torres Strait Islander peoples and communities have control over the collection and management of research materials?	Data are only to be collected and used for the purpose that Aboriginal and Torres Strait Islander store directors/ owners and/or individuals have given written consent for. Consented store directors/owners and individuals have been informed of how the data will be managed. In the final year of the project a governance structure and agreed on protocol to guide future potential use of the project data and the Benchmarking model will be finalised with Aboriginal and Torres Strait Islander stakeholders
9.Was the research guided by an Indigenous research paradigm?	This research has been guided by respect for the rights of store directors/owners to be informed of best-practice health-enabling store policy and practice whilst having the right to determine what policy and practice is best for their store and community. The randomised controlled design of this research suggests a positivist paradigm has guided the research where knowledge is revealed through measurable observation and if it can’t be measured in this way than it is uncertain. However, we are guided in this research by a primary interest in how the co-designed benchmarking strategy can best serve store directors in their effort to contribute to their community’s health. If we find from the effectiveness trial that it does not have the hypothesised impact, then we will seek to understand with Aboriginal and Torres Strait Islander stakeholders how the strategy can be strengthened and what value it has. If the strategy is found to be effective and of value, then we will seek to answer with Aboriginal and Torres Strait Islander stakeholders how it can best be sustained. This research is therefore guided by the belief that there can be many truths that are based on context and peoples’ experiences and that knowledge cannot be separated from context. It also acknowledges that differences in worldviews must be recognised and listened to deeply in order to co-design a strategy that is meaningful for Aboriginal and Torres Strait Islander Peoples and is of value and does no harm to Aboriginal and Torres Strait Islander communities
10.Does the research take a strengths-based approach, acknowledging and moving beyond practices that have harmed Aboriginal and Torres Strait peoples in the past?	This research directly respects Aboriginal and Torres Strait Islander store directors as policy-makers for their store and experts on what works best for their store and community. It also respects partner nutrition practitioners (and their supports) as having the relationships and on-the-ground contextual knowledge needed for delivery of the benchmarking model. The research respects these knowledges and capabilities and is designed to harness and assist these to ultimately support implementation of incremental continuous improvement towards health-enabling best-practice policy and practice
11.Did the researchers plan to and translate the findings into sustainable changes in policy and/or practice?	The research directly plans to delineate how the co-designed benchmarking strategy can be embedded in to ongoing service delivery and policy
12.Did the research benefit the participants and Aboriginal and Torres Strait Islander communities?	This research aims to directly support store directors to adopt best-practice policy and practice for the health of the communities they serve. It will further position Aboriginal and Torres Strait Islander store directors, other community leaders, researchers and health services to advocate for equitable and health-enabling policy and practice for Aboriginal and Torres Strait Islander communities. Wide-scale implementation of best-practice policy and practice across remote stores is likely to significantly impact the excessive burden of diet-related preventable chronic conditions that are disproportionately experienced by Aboriginal and Torres Strait Islander Peoples living in remote communities
13.Did the research demonstrate capacity strengthening for Aboriginal and Torres Strait Islander individuals?	We anticipate that this research in many cases will strengthen store director/owner—nutrition practitioner relationships and strengthen the decision-making capacity of Aboriginal and Torres Strait Islander store directors through the co-design of action plans that respect the needs and aspirations of the store
14.Did everyone involved in the research have opportunities to learn from each other?	There is a strong focus with the benchmarking model on shared learning and for Indigenous and non-Indigenous researchers and partners to have opportunity to learn from each other. The co-design structures particularly foster shared-learning between practitioners, academics, health policy makers and Indigenous and non-Indigenous Peoples. Research dissemination activities including journal and conference publication and this publication protocol encourages all who have had input in to the research to contribute and celebrate in its achievements

